## Abstract

**Background:**

Although previous studies have reported the efficacy of communication skills training (CST) programs, specific training addressing communication about uncertainty and hope in oncology has not yet been studied. This paper describes the study protocol of a randomized controlled trial assessing the efficacy of a CST program aimed at improving physician ability to communicate about uncertainty and hope in encounters with cancer patients.

**Methods/design:**

Physician participants will be randomly assigned in groups (*n* = 3/group) to a 30-h CST program (experimental group) or to a waiting list (control group). The training program will include learner-centered, skills-focused, practice-oriented techniques. Training efficacy is assessed in the context of an encounter with a simulated advanced stage cancer patient at baseline and after the CST for the experimental group, and after four months for the waiting-list group. Efficacy assessments will include communicational, psychological and physiological measures. Group-by-time effects will be analyzed using a generalized estimating equation (GEE). A power analysis indicated that a sample size of 60 (30 experimental and 30 control) participants will be sufficient to detect effects.

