### Study design

Participating physicians will be randomly assigned to either the experimental group or the control group (Fig. 1). After baseline assessment, participants in the experimental group will attend a 4-month training program followed by a post assessment. Participants in the control group will be placed on a waiting list after baseline assessment and will be reassessed four months later. The process of randomization after baseline will allow for a double-blind assessment at baseline.

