#### CST logistics

The CST is a manualized program comprised of ten 3-h sessions (30 h) spread over four to five months. Each training group will include three physicians. The training will be conducted at locations and times choosen by the physicians within each group. The trainer of the experimental group will be an experienced facilitator who will conduct all training sessions ([name]). The training timetable will not include more than two 3-h sessions in one day. Physicians will have the opportunity to register in groups of three or individually. In the latter case, physicians will be assigned to groups according to geographical proximity.

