#### Statistical analyses

The primary outcome of the current study is the physicians’ increased communication performance after training during this encounter. A power analysis has been performed, based on a previous longitudinal study assessing physicians’ communication performance composite score in an encounter with a simulated advanced-stage cancer patient (Mean = 26; SD = 8) [54]. This power analysis was conducted considering 4 independent conditions according to the time (time 1 *versus* time 2) and the group (experimental *versus* control group). As there is no previous study assessing the efficacy of an intensive communication skills training program on physicians’ communication about uncertainty and hope, it was hypothesized that physicians in the control group will maintain a stable performance score from time 1 to time 2. It was also hypothesized that physicians in the experimental group will improve their performance score by 20% from time 1 to time 2. Sample size calculation has been based on an 80% power, a one-sided α = 0.05 t-test and an effect size of 0.65. Considering this power analysis, 60 evaluable physicians are therefore needed for the efficacy assessment. Considering a drop-out rate of 20%, 12 physicians should be moreover recruited (72 physicians in total). It should be recalled at this level that one trainer only will conduct the training of the experimental group. Secondary, to assess also the CST program efficacy, group-by-time effects will be performed using generalized estimating equation (GEE) on psychological, physiological and communicational assessments performed during the encounter with the simulated patient.

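### The stated 80% power treats 60 physicians as independent although they are assigned and trained in groups of three, so it falls short if outcomes correlate within trios

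*Protocol article*

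**What the plan says.** **Allocation.** The Methods/design part of the abstract says: "Physician participants will be randomly assigned in groups", and gives three per group. The Study design section says: "Participating physicians will be randomly assigned to either the experimental group or the control group". It does not mention groups.

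**Delivery.** Under CST logistics: "Each training group will include three physicians". The same section explains how trios form: "Physicians will have the opportunity to register in groups of three or individually". For those who register alone, "physicians will be assigned to groups according to geographical proximity". Each trio shares ten three-hour sessions, and the role-play section has its members rotate through one another's cases. A single trainer serves every trained trio: "one trainer only will conduct the training of the experimental group".

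**Sample size.** Under Statistical analyses: "Sample size calculation has been based on an 80% power, a one-sided α = 0.05 t-test and an effect size of 0.65". The result is 60 evaluable physicians, raised to 72 for drop-out. The four group-by-time cells are treated as independent. No ICC, design effect or number of trios appears.

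**Analysis.** Group-by-time effects are to be assessed with GEE. The unit on which the GEE clusters is not named.

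**The concern.** Three physicians who learn together over ten sessions, give one another feedback and may already be colleagues or neighbours are unlikely to give fully independent outcomes. If whole trios are allocated, pre-existing similarity adds correlation in both arms. If physicians are allocated individually, shared training still induces correlation in the trained arm.

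The variance of the treatment contrast then exceeds what the t-test assumes. Power was set at 80% with nothing to spare, so a null result would come from a trial weaker than reported. A positive result could be challenged on the unit of analysis if the trio were left out of the model. Sixty evaluable physicians make only 20 complete trios, so the number of independent units is small.

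**Working it through.** **Inputs from Statistical analyses.** Mean 26, SD 8, improvement 20%, one-sided α = 0.05, power 80%, 30 evaluable per arm (the split is in the abstract). Trio size 3 is from CST logistics. **Assumed, not in the article:** ICC from 0.01 to 0.20.

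**1. Reproduce the stated figure.** 0.20 × 26 = 5.2, and 5.2 / 8 = 0.65, the stated effect size. For a two-sample t-test the noncentrality is 0.65 / √(1/30 + 1/30) = 2.517 on 58 df. Noncentral-t power is 80.04% at 30 per arm and 78.8% at 29. Sixty is therefore exactly the answer for independent physicians.

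**2. Both arms in trios.** Design effect DE = 1 + (3 − 1) × ICC. Noncentrality = 0.65 / √(2 × DE / 30). With 10 complete trios per arm, df = 20 − 2 = 18.

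**3. Only the trained arm in trios.** Noncentrality = 0.65 / √((DE + 1) / 30). Satterthwaite df come from 9 (10 trios) and 29 (30 individuals), giving 22.8 to 27.2.

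| ICC | DE | Both arms, 18 df | Both arms, 58 df (design effect only) | Trained arm only |
|---|---|---|---|---|
| 0.01 | 1.02 | 77.4% | 79.3% | 78.7% |
| 0.05 | 1.10 | 74.7% | 76.6% | 77.3% |
| 0.10 | 1.20 | 71.4% | 73.4% | 75.5% |
| 0.20 | 1.40 | 65.6% | 67.6% | 72.0% |

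At an ICC of zero, using 18 df alone gives 78.1%, so about two points of the 18-df column come from the degrees of freedom rather than from correlation.

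**4. Incomplete trios.** Recruiting 72 gives 72 / 3 = 24 trios. If drop-out is by individual, 60 evaluable physicians could sit in 24 trios of mean size 60 / 24 = 2.5. With an approximate design effect of 1 + 1.67 × ICC and 22 df, power is 75.8%, 73.0% and 68.0% at ICC 0.05, 0.10 and 0.20.

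**5. Type I error if the trio were ignored.** A physician-level test understates the standard error by a factor 1/√DE. Its true one-sided error is P(Z > 1.645 / √DE), or P(Z > 1.645 / √((DE + 1) / 2)) when only the trained arm is clustered.

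| ICC | SE ratio, both arms | Error, both arms | Error, trained arm only |
|---|---|---|---|
| 0.05 | 0.953 | 5.8% | 5.4% |
| 0.10 | 0.913 | 6.7% | 5.8% |
| 0.20 | 0.845 | 8.2% | 6.7% |

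Simulating an ordinary t-test with 10 trios of three in both arms gives 5.8% at ICC 0.05 and 8.4% at 0.20. An uncorrected sandwich estimator clustered on trio rejects in about 6.5% to 7% of simulated trials. With a small-sample correction and a t reference on 18 df, the rate is about 5.0%.

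**The case against.** - **The analysis is not fixed at physician level.** A reader might infer that the planned analysis will give standard errors that are too small. The article does not support this. GEE is a method for correlated data, its cluster is not named, and an article may leave that detail to a fuller document. This objection stands: the type I error figures are conditional. It does not touch the sample size, which is stated in full.
- **The two allocation statements.** A reader might call them a contradiction. The Study design section is silent on groups; it does not say that physicians are allocated one by one, and the abstract may simply be the more specific text. They still leave the unit of randomisation open and need reconciling.
- **The size depends on an unstated ICC.** This also stands. At 0.01 the design effect alone takes power only to 79.3%, and the loss becomes material from about 0.05 upward.
- **Repeated measures may offset the loss.** The calculation takes no account of pre-post correlation. With a correlation of 0.5, baseline adjustment would multiply the variance by 1 − 0.25 = 0.75, which offsets a design effect of 1 / 0.75 = 1.33, or an ICC of about 0.17. A plain change score has variance 2 × (1 − r) relative to a single measurement: no gain at r = 0.5, and a loss below it. The trial's real power could therefore lie above or below the figures here, so a flat statement that 80% will not be reached goes too far. The stated calculation claims no such credit, however.
- **Higher error rates could be quoted.** An uncorrected z-based physician-level GEE would show somewhat more than step 5, but it already rejects about 5.5% at an ICC of zero. That half point is small-sample bias, not clustering.

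**Conclusion.** The point holds for the sample size. The 60 evaluable physicians are exactly the independent-observations answer, while the article describes assignment and training in threes. On that calculation any positive within-trio correlation takes power below 80%. Over an assumed ICC of 0.05 to 0.20, it is about 75% to 66% with both arms in complete trios (roughly 76% to 68% if drop-out leaves 24 incomplete trios), or about 77% to 72% if only the trained arm is clustered. These figures rest on the assumed ICC, the stated effect size, equal arms and no credit for baseline adjustment.

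The type I error part is conditional. Only if the GEE clusters on the physician would the one-sided error be about 5.8% to 8.4% with both arms clustered, or 5.4% to 6.7% with one.

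**What to change.** 1. Reconcile the abstract and the Study design section so that both state one unit of randomisation.
2. Keep the sample size and restate its power with the design effect over a stated ICC range, giving the number of trios.
3. Name the trio as the cluster in the GEE or in a mixed model, with physician and time nested within it. Use a small-sample correction with a t reference, for example Kauermann-Carroll or Mancl-DeRouen for GEE, or Kenward-Roger for a mixed model. If only the trained arm is grouped, use a partially nested variance structure.

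The cost is a somewhat lower stated power and slightly wider intervals. No further physicians or data are needed.

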**Discussion:**

The current study will aid in the development of effective CST programs to improve physician ability to communicate about uncertainty and hope in encounters with cancer patients.

**Trial registration:**

US Clinical Trials Register NCT02836197.

## Background

Communication with cancer patients poses a variety of widely recognized challenges for physicians. Breaking bad news and explanations of complex treatments must often be relayed so that decisions can be made. It is therefore important for physicians to provide emotional support to patients and their relatives coping with a disease associated with negative outcomes such as treatment side-effects and shortened life-expectancy. It is important to underline that current cancer treatments are increasingly personalized and based on multidisciplinary approaches [1–3]. Due to medical progress, cancer patients are living longer with their disease, posing new challenges in doctor-patient communication to help patients cope with uncertainty and to promote hope.

Prior studies have indicated that cancer patients have an expectation that physicians will discuss uncertainty and hope [4] to help them adjust to their diagnosis [1, 5, 6] and to maintain hopefulness [7–9]. Moreover, patients wish for realistic, individualized, full and honest information regarding their current medical condition and prognosis [8, 10–14]. These studies suggest that physicians who communicate about uncertainty and hope are meeting patient expectations.

The current models of communication in healthcare advocate the use of general uncertainty management skills during physician communication with cancer patients [15, 16] and assumes that physicians must promote patient hope [17]. Models of coping with cancer [5] argue that communication between physicians and patients about uncertainty may improve patient adjustment to their illness. According to these models, communication about uncertainty and hope will benefit patient quality of life, help the patient maintain a positive outlook and will decrease conflict between physicians and patients when making decisions [1, 17, 18]. These models underline the importance of effective communication skills between physicians and their cancer patients concerning uncertainty and hope [17, 19].

However, due to a lack of specific medical training, physicians often report a negative perception about the outcome of discussing uncertainty and hope with cancer patients [20]. Physicians fear these discussions will lead to unrealistic expectations leading to additional stress on the patient’s condition [20]. In addition, physicians are leery of increasing patient concerns that will be difficult to manage. As a consequence, physicians experience difficulties and can be reluctant to communicate about uncertainty and hope with cancer patients [21–24], fearing that addressing these issues will lead to increased work stress [25].

Poor communication about uncertainty and hope in encounters with cancer patients may lead to negative outcomes for both patients and care providers [25–27]. For cancer patients, poor communication may be detrimental to illness adjustment [28] and may lead to inadequate strategies such as searching certainty, resulting in conflicts with healthcare professionals [29]. For healthcare providers, poor communication may result in a lack of work satisfaction [30], higher risk of burnout [25], higher use of healthcare services [31], increased costs, [25] and decreased quality of care delivery [32]. Studies assessing training methods that may help physicians overcome communication difficulties about uncertainty and hope is thus needed.

Previous studies have reported on the efficacy of communication skills training (CST) programs in the improvement of low- to middle-level communication skills of physicians such as breaking bad news to cancer patients, assessing psychosocial issues and talking with patient relatives [33]. CST programs have used learner-centered, skill-focused and practice-oriented techniques resulting in improvements in physician communication and support skills [34–37], attitudes toward psychosocial and emotional issues [30, 38–41], empathy toward patients [38, 39, 42] and work satisfaction [36]. In addition, these programs have benefited patients by decreasing anxiety [43] and increasing satisfaction [44, 45]. Taken together, the results from these studies have confirmed the usefulness of CST programs offered in small groups (maximum of six participants) over the course of a minimum of 20 h.

The efficacy of CST programs aimed at improving physician communication skills on the topics of uncertainty and hope has not yet been studied [1, 46]. These topics require specific CST. Communicating with patients about uncertainty implies a deep assessment of patient expectations about the future and informing patients about uncertainties. Communication of hope requires a deep understanding of patient wishes for the future while supporting ways needed to achieve them [47]. This collaborative and bidirectional process of communication between physician and patient on sensitive topics associated with the patient’s medical, psychological and social future will ultimately benefit both patient and physician.

## Methods/design

### Aim of the trial

A randomized longitudinal study assessing the efficacy of a CST program aimed at improving physician communication about uncertainty and hope with cancer patients will be conducted. Efficacy of the program will be assessed by the analysis of changes over time in physician communication skills and physician psychological and physiological health. These assessments will be performed in the context of an encounter with a simulated advanced-stage cancer patient.

### Subjects

Participants will be physicians that are specialists or residents, have a practice including cancer patients and speak French. The study was approved by a central ethics committee (Jules Bordet Institute, Cancer Center of the Université Libre de Bruxelles) and all participants will provide written informed consent.

### Study design

Participating physicians will be randomly assigned to either the experimental group or the control group (Fig. 1). After baseline assessment, participants in the experimental group will attend a 4-month training program followed by a post assessment. Participants in the control group will be placed on a waiting list after baseline assessment and will be reassessed four months later. The process of randomization after baseline will allow for a double-blind assessment at baseline.

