**Fig. 1 Fig1:**
[figure not shown]
Study Design. Physicians will be randomly assigned to 30-h CST program (*experimental group*) or to a waiting list (*control group*). Training efficacy is assessed in the context of an encounter with a simulated advanced stage cancer patient at baseline and after the CST for the experimental group, and after four months for the waiting list group. Communicational, psychological and physiological assessments will be conducted

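### The protocol gives two training lengths and times the second assessment differently by arm, so trained physicians may be reassessed up to one month later than controls

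*Protocol article*

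**What the plan says.** The Study design section sets the timing for both arms. For the experimental arm: "After baseline assessment, participants in the experimental group will attend a 4-month training program followed by a post assessment". For the control arm: "Participants in the control group will be placed on a waiting list after baseline assessment and will be reassessed four months later".

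The legend of Fig. 1 places the efficacy assessment "at baseline and after the CST for the experimental group, and after four months for the waiting list group", and the abstract says the same. The second assessment is therefore tied to an event (the end of training) in one arm and to a fixed elapsed time in the other.

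The CST logistics section describes the same programme with a different length: "The CST is a manualized program comprised of ten 3-h sessions (30 h) spread over four to five months". It also lets each group set its own timetable: "The training will be conducted at locations and times choosen by the physicians within each group".

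In the Statistical analyses section, the power analysis assumes no change without training: "it was hypothesized that physicians in the control group will maintain a stable performance score from time 1 to time 2". For the trained arm it assumes that "physicians in the experimental group will improve their performance score by 20% from time 1 to time 2".

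**The concern.** The waiting list is there to show what untrained physicians would score at the time when the trained physicians are assessed again. That works best when both arms have the same time between assessments. Here the control interval is a constant and the experimental interval depends on how long training takes, for which the article gives two values. On the longer value, part of the experimental arm is reassessed later than every control seen on schedule.

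Anything that moves scores with time since baseline would then act for longer in one arm. The participants include residents, who may gain experience month by month. Only one simulated case is described, so it appears to be used at both assessments (this is implied, not stated), and memory of it may fade. The two mechanisms pull in opposite directions: added experience would inflate the apparent training effect, and fading memory could shrink it.

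At stake is whether a small part of the group-by-time contrast reflects elapsed time and not training.

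**Working it through.** **Step 1: the plan's own sample size.** This point disputes no computed figure, but the planned effect is needed as a yardstick. Inputs from the Statistical analyses section: mean 26, SD 8, improvement 20%, and "Sample size calculation has been based on an 80% power, a one-sided α = 0.05 t-test and an effect size of 0.65".

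- Target difference: 0.20 × 26 = 5.2 points.
- Effect size: 5.2 / 8 = 0.65, as stated.
- A one-sided two-sample comparison at α = 0.05 and 80% power gives 30 per arm, 60 in total, as stated. The noncentral t distribution with 30 per arm gives 80.0% power.

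The figure of 60 reproduces, and nothing below changes it.

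**Step 2: the intervals side by side.**

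| Source for training length | Experimental interval | Control interval | Difference |
|---|---|---|---|
| Study design | 4 months | 4 months | 0 |
| CST logistics, lower end | 4 months | 4 months | 0 |
| CST logistics, midpoint (assumed average) | 4.5 months | 4 months | 0.5 month (0.5 / 4 = 12.5%) |
| CST logistics, upper end | 5 months | 4 months | 1 month (1 / 4 = 25%) |

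The planned difference is 0 to 1 month, and no row makes the control interval the longer one. Any wait between baseline and the first session, or between the last session and the post assessment, would lengthen the experimental interval further. The article gives no figure for such waits, so they are left out.

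**Step 3: from interval to score.** The bias is the monthly change in an untrained score multiplied by the extra months. The document gives no monthly change. It assumes stability, and then the bias is 0 × (0 to 1) = 0. To show the scale under other values, assume an absolute drift of 0.1 to 1.0 point per month (an assumption, not from the document):

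| Assumed drift (points per month) | Bias at 0.5 month | Bias at 1 month | Share of 5.2 points at 1 month |
|---|---|---|---|
| 0.1 | 0.05 | 0.1 | 1.9% |
| 0.25 | 0.125 | 0.25 | 4.8% |
| 0.5 | 0.25 | 0.5 | 9.6% |
| 1.0 | 0.5 | 1.0 | 19.2% |

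The last column takes the largest planned mismatch for every trained physician, so it is an upper bound for each assumed drift. The sign is open, because the mechanisms named above work in opposite directions.

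**The case against.** The strongest reply is that the Study design section, read alone, has no imbalance: four months of training followed by assessment, and four months for controls. The arms are then nominally matched, and a difference appears only if the upper part of the range under CST logistics applies. This stands. A reader might infer that follow-up differs systematically between arms as an established fact, but the document does not support that. What it establishes is a contradiction about training length, one reading of which produces the difference.

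A second reply is that assessment windows are commonly left to the full protocol, which is not shown. That is right about missing windows, but it does not answer this point, which rests on what the article states: two lengths for one programme, and two different anchors for the second assessment.

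A third reply is that the mechanisms are weak. Much of this stands. Drift in the actress's performance is a tempting addition, but the Simulated patient encounter section provides a standardised script and regular feedback sessions. Such drift would also follow the calendar date and not each physician's time since baseline, so it need not align with arm. The share of residents is not given, and nothing shows that one more month of practice, or of forgetting, moves the score materially.

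Finally, a reader might infer that the gap can exceed one month or that delay always falls on one arm. The stated range includes zero, no further delay is specified, and controls can also be seen late. Only the planned interval is one-directional.

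**Conclusion.** The point holds as an internal contradiction with a modest consequence. The article describes the programme as lasting four months in one section and four to five months in another. It fixes control reassessment at four months, while the experimental arm is reassessed when training ends. If the longer range applies, the experimental interval exceeds the control interval by 0 to 1 month (0 to 25%), and elapsed time is partly confounded with arm.

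The effect on the score cannot be computed from the document. It is probably small against the 5.2-point target, and it is zero under the protocol's own assumption of stable control scores. That assumption is not a full defence, because a concurrent control arm is there so that the comparison need not depend on it.

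It would go too far to conclude that the control arm no longer gives a usable comparison. A planned mismatch of at most one month, with no documented drift, does not support that. The sample size is not affected.

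**What to change.** Reconcile the Study design and CST logistics sections so that the article gives a single statement of training length. Then set the same reassessment window after baseline for both arms. One way is to schedule control reassessments over the same four-to-five-month span in which the experimental groups finish training, if that span is the one retained. The planned difference between arms then becomes zero. Report the observed interval from baseline to reassessment by arm, so that readers can see whether the match was achieved.

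Adjusting for days since baseline is not a good substitute. With controls fixed at four months, the interval would vary almost only within the trained arm. It would be close to collinear with arm, and its slope would mix elapsed time with session spacing that the groups chose themselves.

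The cost is scheduling only: some controls may wait up to about one more month for reassessment.
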